4.1 The designs of clinical research

A case-control study conducted with JMDC co, Ltd,.

4.2 Procedure

This study was conducted in collaboration with JMDC Corporation, a company whose main business is to provide medical statistics data services by maintaining receipts (inpatient, outpatient, and dispensing) and medical examination data from multiple health insurance associations.

The data has been accumulated since 2005, and the cumulative population is approximately 5.6 million as of June 2018. About 4,000 target cases are extracted from the database (anonymized processed information) held by JMDC, using extraction criteria. JMDC will construct analysis data from the clinical information, and conduct statistical analysis of the onset and relapse factors of Crohn's disease from the constructed analysis data.

A validity evaluation of the inclusion criteria will be also conducted. JMDC, Inc. will extract the 400 cases of patients in Kitasato University Kitasato Institute hospital to be used for the validity evaluation. JMDC will extract a total of 400 patients who meet and do not meet the criteria from the receipts held by the hospital, and anonymize them by assigning a research number to the research subject so that no specific individual can be identified at this facility (Correspondence table provided by [name], Personal Information Manager). The corresponding table will be kept in a locked cabinet by the principal investigator, and the information will not be taken outside the facility. Cases will be selected from the anonymized data according to the inclusion criteria, and random sampling will be conducted. A medical chart review to determine whether the cases had Crohn's disease was conducted by a research physician. Based on the results of the medical record review, the validity of the inclusion criteria will be assessed by calculating the positive/negative predictive value, sensitivity, and specificity.

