2.1 Inclusion criteria

Extract the following patients from the database held by JMDC Corporation.

① Patients diagnosed with CD using ICD-10 coding of K50 (Appendix 1).

② Patients diagnosed with CD using the ICD-10 coding of K50 (Appendix 1).

In addition to (1) and (2) above, patients who, within ±12 months from the date of diagnosis, have prescribe code or procedure code listed in the national guidelines for Crohn's disease. (Reference 1)

③Patients who do not meet the above criteria.

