 2.3 Patients for inclusion criteria validity assessment

Patients who visited Kitasato University Kitasato Institute Hospital from May 1, 2012, to March 31, 2019, and meet the following criteria will be eligible.

(1) 100 cases each of patients who meet the inclusion criteria ① and ②

(2) 200 cases of patients who meet ③

3. Informed consent

Since this research uses receipt data and medical records, no written explanation or consent will be obtained by the "Ethical Guidelines for Medical and Health Research Involving Human Subjects”. By this guideline, informed consent was obtained in the form of opt-put on the web-site. In this way, patients or surrogates patients who refuse to participate in the study will be removed from the analysis and immediately disposed of.

4. Methods of clinical research

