5.2 Secondary endpoints

The validity of the extraction conditions (positive predictive value, negative predictive value, sensitivity, specificity).Report on deviations from the implementation plan

The principal investigator must obtain prior approval from the Kitasato Research Institute Hospital Research Ethics Committee before implementing the clinical research protocol. Besides, it is prohibited to deviate from or change the in the event of any deviation from the clinical research protocol, the principal investigator shall notify the investigator of the deviation. (2) The researcher shall record all of the following information, along with the reasons for it, and report it to the Research Ethics Committee.

7. discontinuation and dropout criteria

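### Sensitivity and specificity are listed as validity measures, but charts are sampled by quota on the claims result, so both depend on the quota unless weighted to hospital totals

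*Protocol*

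**What the plan says.** Section 2.1 describes patients identified by a Crohn's disease code, a narrower group who also have a guideline drug or procedure code within 12 months of diagnosis, and a remainder: "③Patients who do not meet the above criteria".

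Section 2.3 sets the chart sample by membership of these groups: "100 cases each of patients who meet the inclusion criteria ① and ②" and "200 cases of patients who meet ③". Section 4.2 repeats the total: "JMDC will extract a total of 400 patients who meet and do not meet the criteria from the receipts held by the hospital". It adds that sampling is random and that a physician decides from the chart whether the patient had Crohn's disease. On that basis, "the validity of the inclusion criteria will be assessed by calculating the positive/negative predictive value, sensitivity, and specificity".

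Section 5.2 gives the secondary endpoint as "The validity of the extraction conditions (positive predictive value, negative predictive value, sensitivity, specificity", closing the list there. The sample-size paragraph after section 10 justifies the quotas by the precision of a PPV of 80% (95% CI ±0.1) and by nothing else. Section 1 states the aim of the chart review in terms of predictive values only.

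The protocol gives no count of hospital patients in each group, no sampling fraction and no weighting.

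**The concern.** PPV and NPV condition on the claims result, which is what the sample is drawn on. A random sample within a claims group therefore estimates them directly. Sensitivity and specificity condition on true disease, and each takes its numerator and the rest of its denominator from different claims groups. If those groups are sampled at different rates, the ratio in the charts is not the ratio in the hospital. Random sampling within each group does not cure this.

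The usual direction is predictable. When criteria-negative patients are sampled at a much lower fraction than criteria-positive ones, false negatives and true negatives are under-represented, so sensitivity comes out too high and specificity too low. A sensitivity near 99% would be read as evidence that the claims definition misses almost no Crohn's disease. The charts alone could not support that.

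**Working it through.** **Inputs.** From the protocol: quotas of 100 (①), 100 (②) and 200 (③), and a PPV of 80%. Not in the protocol, and varied here as assumptions: the NPV and the hospital counts. The tables below use one criteria-positive group at a time against ③. They fit definition ① if its 100 charts are drawn at random from everyone meeting ①.

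**The plan's own figure.** The simple precision formula gives n = 1.96² × 0.80 × 0.20 / 0.10² = 61.5, so 62 charts. The protocol says 100, which gives ±0.078 at a PPV of 80%. The quota is therefore ample for PPV. That mismatch is a separate matter and nothing below depends on it. The 200 charts for ③ have no stated basis in NPV or sensitivity.

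**Step 1: change only the quota.** With n₊ criteria-positive and n₋ criteria-negative charts:

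- TP = n₊ × PPV and FP = n₊ × (1 − PPV)
- TN = n₋ × NPV and FN = n₋ × (1 − NPV)
- sensitivity = TP/(TP + FN) and specificity = TN/(TN + FP)

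Take PPV 80% and an assumed NPV of 99.5% (1 missed case in 200):

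| Quota | TP | FP | FN | TN | Sensitivity | Specificity |
|---|---|---|---|---|---|---|
| 100:200 | 80 | 20 | 1 | 199 | 80/81 = 98.8% | 199/219 = 90.9% |
| 200:200 | 160 | 40 | 1 | 199 | 160/161 = 99.4% | 199/239 = 83.3% |
| 100:1000 | 80 | 20 | 5 | 995 | 80/85 = 94.1% | 995/1015 = 98.0% |

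The definition, PPV and NPV are the same in every row. No hospital figure is needed to show the dependence.

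**Step 2: weight back to assumed hospital counts.** Each chart is weighted by stratum total / charts reviewed. Assume 500 criteria-positive patients, so TP = 400 and FP = 100. Let N₃ be the number of patients in ③, so FN = N₃/200.

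| N₃ (assumed) | FN | TN | Weighted sensitivity | Weighted specificity |
|---|---|---|---|---|
| 5,000 | 25 | 4,975 | 400/425 = 94.1% | 4,975/5,075 = 98.0% |
| 10,000 | 50 | 9,950 | 400/450 = 88.9% | 9,950/10,050 = 99.0% |
| 50,000 | 250 | 49,750 | 400/650 = 61.5% | 49,750/49,850 = 99.8% |

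The raw figures are 98.8% and 90.9% in all three rows. They would be right only if the hospital's ratio of criteria-positive to ③ patients happened to be 1:2, that is N₃ = 1,000 for 500 positives.

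**Separate note on precision.** If none of the 200 ③ charts shows Crohn's disease, raw and weighted sensitivity are both 100%, so the quota adds no bias to sensitivity. But the exact 97.5% upper limit for missed cases in ③ is 1 − 0.025^(1/200) = 1.83%. With 500 positives, that limit is compatible with a sensitivity as low as 400/(400 + 0.0183 × N₃): 81%, 69% or 30% for the three values of N₃.

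**The case against.** The best defence is that the protocol names four measures without saying that they will be read unweighted from the 400 charts. An estimator is commonly left to a statistical analysis plan, which may exist and is not shown. The provider works from the hospital's receipts, so stratum totals should be obtainable. A reader might infer that biased figures are certain to be published; the documents do not show that. What remains is that the protocol itself pairs a quota design with measures that design cannot deliver directly. It specifies extraction of 400 patients with no totals. Weights added later would need counts that the protocol does not ask anyone to record, and section 17.4 has the provider delete its constructed data when the study ends.

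Three other stronger readings also go too far:

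- **That the raw figures reflect the quota and say nothing about the criteria.** They depend on the quota together with PPV and NPV.
- **That the hospital's coded patients are mostly sampled and other visitors hardly at all.** This is plausible in direction, but no hospital count is given. Under the 500 assumed above, 100 charts are only 20%.
- **That the study's main result is at risk.** The primary endpoint (section 5.1) concerns risk factors. The chart-review aim in section 1 and the sample-size basis rest on predictive values, which the design can estimate.

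**Conclusion.** The point stands in limited form. The chart sample supports PPV, and NPV for patients meeting neither criterion. It does not support sensitivity or specificity unless the charts are weighted to stratum totals that the protocol does not collect.

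The dependence on the quota follows from the design and needs no hospital figures. The size of the distortion does need them: the gap in sensitivity runs from 4.7 percentage points (98.8% against 94.1%) to 37 points (98.8% against 61.5%) over the assumed range, and also rests on an assumed single false negative in 200. Two of the four measures within one secondary endpoint are affected. This should be corrected before the validity results are calculated, but it does not call the study as a whole into question.

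**What to change.** 1. In sections 4.2 and 5.2, make PPV and NPV the validity measures estimated directly from the charts.
2. Settle what separates ① from ②. As printed in section 2.1 the two code criteria are almost the same, and ② appears to be nested in ①, so the two chart samples may overlap.
3. Have the database provider record, for the hospital receipts from May 2012 to March 2019, the number of patients in non-overlapping strata: meets ②; meets ① but not ②; meets neither. Record the stratum of each sampled chart.
4. Calculate sensitivity and specificity separately for ① and ②, weighting each chart by stratum total / charts reviewed. For ②, patients meeting ① only count as criteria-negative, for NPV as well, so comparing ② with ③ alone is not enough.
5. Use an interval that stays valid with zero false negatives, for example by carrying exact or score limits for the ③ stratum through to sensitivity. A plain bootstrap or delta method collapses to zero width there.
6. If the counts cannot be supplied, delete sensitivity and specificity.

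The cost is a short protocol amendment, a few counts and a weighted calculation, with no extra charts. The sensitivity interval will be wide, which is a fair picture of what 200 criteria-negative charts can show.

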4.3 Data Management

The analysis data extracted from the hospital's receipt information will be stored appropriately in JMDC's information system in accordance with JMDC's information security rules in compliance with ISMS (Contact: [name]). The correspondence chart will be strictly managed by [name], the personal information manager in the hospital.

4.4 Case Registration Method

Extract the following information about the target case.

1) Date of diagnosis of Crohn's disease

2) Patient background (gender, age, height, weight, medical history, family history, current medications, and (Crohn's disease, time of onset (disease duration), disease type)

3) Presence or absence of complications such as anal lesions, stenosis, fistula, skin, arthritis, etc.

4) Lifestyle factors such as alcohol consumption and smoking habits before the onset of Crohn's disease

5) Lifestyle factors such as alcohol consumption and smoking habits after the onset of Crohn's disease

6) Therapeutic drugs (mesalazine, steroids,

immunomodulators, biologics) (Drugs listed in the diagnostic criteria and treatment guidelines for Crohn's disease*1 such as

(7) NSAIDs, antibacterials, statins, oral contraceptives, and other drugs related to the onset and relapse of Crohn's disease. History of use of the drug to be given

8) Availability and date of surgery

9) Hospitalization and date

10) Presence and date of malignancy in and outside the intestinal tract 5. evaluation items

 5.1 Primary endpoints

Evaluation of risk factors associated with the development of Crohn's disease and relapse.

5.2 Secondary endpoints

The validity of the extraction conditions (positive predictive value, negative predictive value, sensitivity, specificity).Report on deviations from the implementation plan

The principal investigator must obtain prior approval from the Kitasato Research Institute Hospital Research Ethics Committee before implementing the clinical research protocol. Besides, it is prohibited to deviate from or change the in the event of any deviation from the clinical research protocol, the principal investigator shall notify the investigator of the deviation. (2) The researcher shall record all of the following information, along with the reasons for it, and report it to the Research Ethics Committee.

7. discontinuation and dropout criteria

 7.1 Discontinuation of enrolled patients

There are no dropout criteria for this study, but since it is conducted using an opt-out

Patient data that have been requested not to participate in the study by opting out will be used for data extraction.

Excluded at the time of data extraction. Requests made after data extraction will be excluded from published materials.

7.2 Stopping the research itself

When the principal investigator decides that the research should be discontinued.

In the above cases, report to the hospital director and the Kitasato Research Institute Hospital Research Ethics Committee.

8. expected adverse events and emergency reporting methods In this study, we extracted and analyzed anonymized information from the medical fee database.

This is a study without medical intervention. No expected adverse events are expected.

9. analysis method

(1) Analysis target

All enrolled patients will be included in the analysis.

(2) Statistical analysis

Perform statistical analysis using the following methods, as appropriate.

Contingency table analysis: χ-square test, Fisher's exact test Comparison of two unpaired groups: unpaired t-test, Mann-Whitney U test.

Correspondence between two groups: Correspondence t-test, Wilcoxon sign rank test.

Survival time analysis: Cox regression analysis, Log-rank test Multivariate analysis: Logistic Regression Analysis

(indicating an approximate quote or vague suggestion) or something.

(3) Person responsible for analysis

[name], Deputy Director, Center for Advanced Inflammatory

7

Bowel Disease, Kitasato Institute Hospital, Kitasato University

(4) Evaluation of analysis results

The results of the analysis will be published after evaluation by the Center for Advanced Therapy of Inflammatory Bowel Disease.

10. expected research period

Case accumulation period: After approval by the director of the institution - September 30, 2020 (A.D.)

Validity evaluation period: After approval by the director of the institution - September 30, 2020 (A.D.)

Case analysis period: After approval by the director of the institution - March 31, 2021 (A.D.)

The number of cases to be studied and the basis for setting the number (1) Number of cases to be studied The expected number of cases is the total number of Crohn's disease cases recorded in the JMDC database target.

The number of cases required for validity assessment is 100 cases for criteria (1) and (2), and 200 cases for (3). (2) The basis for setting if the positive predictive value is set at 80% (95% confidence interval ± 0.1), the sample size required for validity assessment is 100 cases or criteria (1) and (2), and 200 cases for (3).

However, research funds are subject to review by the Kitasato University Conflict of Interest Review Committee. It is properly managed, and the researcher must use his or her professional judgment for personal gain. There is no such thing as bending the rules. 16.2 Compensation for Health Damage. This research is a case-control study using receipt information and medical information not applicable.

17. ethical matters

17.1 Compliance with Ethical Guidelines and Declaration of Helsinki

This research will be conducted in compliance with the latest "Declaration of Helsinki" and "Ethical Guidelines for Medical Research Involving Human Subjects," etc.

17.2 Review and Approval by the Ethics Committee

 This clinical research will be started after approval by the Research Ethics Committee and permission by the head of the institution.

17.3 Informed Consent

 Since this research uses receipt data and medical records, no written explanation or consent will be obtained in accordance with the "Ethical Guidelines for Medical Research Involving Human Subjects. In order to disclose the "matters that should be disclosed regarding the conduct of the research in the event that informed consent is not obtained" as indicated in the guidelines and to give the subject or a substitute the opportunity to refuse to participate in the research, materials regarding opt-out will be posted, and the data of subjects who refuse to participate in the research will be deleted from the analysis and immediately destroyed. The data of subjects who refuse to participate in the study will be removed from the analysis and immediately destroyed.

17.4 Protection of Personal Information and Disclosure of Data

JMDC Inc. will extract cases from the hospital's receipt information, anonymize the data so that no specific individuals can be identified, and construct the data, but the corresponding tables will be kept in strict confidence at the hospital. JMDC will delete the constructed data as soon as the study is completed. JMDC will delete the data as soon as the study is completed. The results of this study will be published in academic journals, but no personally identifiable information will be disclosed. The data obtained in this study will not be used for any other purpose than this study.

18. Publication of research results and attribution of intellectual property rights

Research results will be used as materials for conference presentations, academic information provision, etc. The research results will be presented at academic conferences and published in academic journals and databases within one year of the completion of the research.

19. Changes to the implementation plan, etc.

 Any changes (revisions) to the research protocol must be approved by the Research Ethics Committee in advance.

References

1. Ministry of Health, Labour and Welfare, "Survey and Research on Intractable Inflammatory Bowel Ginger" (Suzuki Group)

Diagnostic criteria and treatment guidelines for ulcerative colitis and Crohn's disease, revised in 2008

21. appendix

 Appendix 1 ICD-10 codes used for extraction criteria K50.0 Crohn's disease of small intestine

 Crohn's disease of the ileum

 Crohn's disease of the jejunum

 Crohn's disease of the duodenum

 Crohn's disease of the small intestine

K50.1 Crohn's disease of large intestine

 Crohn's disease of the colon

 Crohn's disease of the appendix

 Crohn's disease of the rectum

K50.8 Other Crohn's disease

 Gastric Crohn's disease

 Gastroduodenal Crohn's Disease

 Crohn's disease of the anus

 Crohn's disease of small and large intestine K50.9 Crohn's disease, details unknown.   Crohn's disease

 Crohn's Juvenile Arthritis

 Steroid-Dependent Crohn's Disease
